### **Administered Pre-Intervention Only:**

Demographics – covariates and moderators

### **Administered Pre-Intervention, Post-Intervention, 6 and 12 Month Follow-Ups:**

Quality of Life (WHOQOL-BREF) physical health scale – co- primary outcome.

Quality of Life (WHOQOL-BREF) psychological scale – co- primary outcome.

Quality of Life (WHOQOL-BREF) social relationships scale – secondary outcome.

Quality of Life (WHOQOL-BREF) environmental scale – secondary outcome.

The Patient-Health Questionnaire Depression (PHQ-9) – secondary outcome/mediator

The Generalized Anxiety Disorder Questionnaire (GAD-7) – secondary outcome/mediator

MOS Social Support Survey – secondary outcome/mediator

The Gratitude Questionnaire Six Item Form (GQ-6) – secondary outcome/mediator

Revised Life Orientation Test (LOT-R) – secondary outcome/mediator

Measure of Current Status Part A (MOCS-A) – secondary outcome/mediator

Cognitive and Affective Mindfulness (CAM) – secondary outcome/mediator

Perceived Stress Scale 10 (PSS-10) – secondary outcome/mediator

Interpersonal Reactivity Index (IRI) Empathic Subscale – secondary outcome/mediator

PROMIS Pain Interference v8 – secondary outcome/mediator

Graded Chronic Pain Scale (GCPS) – secondary outcome/mediator

# MIND-BODY SKILLS TRAINING FOR ADULTS WITH NEUROFIBROMATOSIS

Patient Homework –weekly during intervention:

Progress Note – adherence to treatment/skill consolidations/moderator.

Administered Post-Intervention, 6 and 12 Month Follow-Ups Only:

Patient Perception of Improvement – anchor-based measure of improvement

Figure 1. Study Design.

[figure not shown]

## VI. BIOSTATISTIC ANALYSIS

**1. Missing data:** We will assess for patterns of missing data, which are expected to be low as the study uses computer-assisted questionnaire completion (REDCap), which reduces participant non-response (see how missing data is handled below). The primary anticipated reason for missing data is attrition due to loss of follow up. Based on our preliminary studies, in particular our videoconferencing RCT, we do not anticipate loss of data at time 2 (100% observed retention). However, we do anticipate some loss of data for the 6 (82.5% observed retention) and 12 months follow up. Conservatively, we estimate up to 5% loss to follow-up by post-treatment and up to 20% loss to follow-up by 12 months. Hence, we plan to enroll 224 participants to achieve at least 212 at post-treatment and 180 at 6 and 12 months. We will use mixed-model maximum-likelihood techniques for analysis to minimize bias when lost to follow-up is missing at random conditional on the observed data. Attrition effects will be evaluated by testing whether systematic differences exist between those participants who completed the research versus those who drop out. In this way we can determine the nature of the potential bias introduced by study attrition. If attrition is higher in the 3RP-NF group, multiple imputation and sensitivity analyses assuming a range of informative loss to follow-up will be investigated. Note that in our preliminary study, drop-out was more common in the placebo arm, which if it reflects lack of efficacy would yield conservative estimates of benefit from 3RP-NF.

**2. Evaluating possible confounders:** In the preliminary analyses we will examine the equivalence of the random assignment of groups with regard to key baseline characteristics. This will involve assessment of the treatment groups on sociodemographic characteristics, psychosocial variables and homework completion. In the unlikely event that important differences at baseline occurred by change even with randomization, we will run analyses both with and without these variables as covariates to determine whether baseline differences may account for differences in outcomes.

**3. Analyses for primary aim –Specific Aim 1:** Data analyses will follow a sequence that is designed to answer the primary question: Does the 3RP-NF intervention improves physical and psychosocial quality of life (co-primary outcomes), social quality of life, environmental quality of life, pain intensity, pain interference, depression and anxiety (secondary outcomes) relative to the comparison condition HEP-NF? We have already established feasibility and acceptability of the 3RP-NF, so the emphasis of this study is on establishing the efficacy (primary time point at

post-intervention) and durability (to 6 and 12 months) of the 3RP-NF. Accordingly, the primary analysis will compare changes in primary and secondary outcomes (continuous measures) from baseline to the post-, 6 months and 12 months visits between the randomized conditions. All randomized participants will be included in our primary efficacy analyses as randomized, following the intention-to-treat principle. Data will be analyzed using a shared-baseline, linear mixed model with fully unstructured covariance among repeated measures. The shared-baseline assumption reflects the true state of the population prior to randomization and has the benefit of adjusting for chance differences at baseline. For each outcome, we will compare the effect of 3RP-NF vs. HEP-NF on changes from baseline to the post-test, 6 and 12 months follow-up times using linear contrasts. Our primary aim will focus on the post-treatment follow-up time. With two co-primary outcomes, we will use two-sided tests at  $p < 0.025$  to declare superiority of 3RP-NF, maintaining an overall 5% type 1 error at our primary post-intervention time point. Persistence of a benefit from 3RP-NF at 6 and 12 month follow-up times will be analyzed as a non-inferiority test of durability. Non-inferiority of 3RP-NF in maintaining benefits relative to HEP-NF will be declared if the lower one-sided 95% confidence bound for a given co-primary outcome is less than 6.25 units (the estimated MCID) in favor of HEP-NF. Several sensitivity analyses will be explored using alternative models. Change scores at post-intervention, 6 months, and 12 months will be separately analyzed by Wilcoxon rank sum test to avoid any parametric assumptions about the data. More parsimonious covariance structures will be considered using random participant-specific intercepts, slopes, and quadratic terms (i.e., growth curve analysis). Baseline parameters such as NRS pain will be included to account for chance differences due to randomization and to explain sources of variation in response that are independent of treatment group.

While no information on clinically meaningful differences exists for the primary outcome measures for patients with NF, we will also use both “distribution-based” and “anchor-based” methods as criteria to determine important change. Consistent with “anchor based” methods, we will ask patients at post-treatment, 6 and 12 months follow ups to rate whether they were “substantially better”, “minimally better” “about the same”, “minimally worse” or “substantially worse” as compared to how they were before the intervention. These improvement ratings would thus serve as the standard with which to evaluate the importance to the patient of whatever changes in quality of life occurred during the intervention. Success of the trial will thus be estimated based on outcome score (quality of life scores) and anchor-based measures of subjective improvement. The anchor-based MCID estimates will be computed using prior methodology, as the mean change in the physical health and psychological health QoL among those in the “minimally better” category.

**3.1. Power Consideration and Sample Size Calculations.** The effective standard deviation (SD) for the change from baseline to post-treatment in QoL Physical and QoL Psychological based on a repeated-measures ANOVA of our preliminary data was 14.7 and 10.4 units, respectively. The effective SD from post-treatment to 6-month follow-up was 11.4 and 10.0 units, respectively. Based on these estimates, assuming an MCID of 6.25 units, allowing up to 5% loss to follow-up by post-treatment assessment, and testing each of the co-primary outcomes at  $p < 0.025$  two-sided, the study will have 80% power for QoL Physical and 96% power for QoL Psychological. Allowing up to 20% loss to follow-up by the 6-month assessment, the study will have 99% power to declaring non-inferiority of 3RP-NF vs. HEP-NF if the true treatment-dependent difference in maintenance of any change from baseline to post-treatment is zero.

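### Informative-dropout analyses are planned only if 3RP-NF loses more participants, yet equal or control-heavy dropout can also bias the 6- and 12-month durability contrasts towards 3RP-NF

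*Protocol*

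**What the plan says.** Section VI.1 of the protocol takes a missing-at-random mixed model as the main analysis: "mixed-model maximum-likelihood techniques for analysis to minimize bias when lost to follow-up is missing at random conditional on the observed data". It foresees the following losses: "we estimate up to 5% loss to follow-up by post-treatment and up to 20% loss to follow-up by 12 months". The enrolment target follows from these: "we plan to enroll 224 participants to achieve at least 212 at post-treatment and 180 at 6 and 12 months".

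One check is always made: "Attrition effects will be evaluated by testing whether systematic differences exist between those participants who completed the research versus those who drop out". The analyses that allow for informative loss are conditional: "If attrition is higher in the 3RP-NF group, multiple imputation and sensitivity analyses assuming a range of informative loss to follow-up will be investigated". The reason offered for looking in one direction only is that, in the pilot, "drop-out was more common in the placebo arm, which if it reflects lack of efficacy would yield conservative estimates of benefit from 3RP-NF".

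Section VI.3 tests durability at 6 and 12 months as non-inferiority, using a one-sided 95% confidence bound and a margin of 6.25 units. It also lists sensitivity analyses that do not depend on attrition: Wilcoxon tests, simpler covariance structures and baseline covariates. None is described as addressing informative loss.

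**The concern.** The trigger is the sign of the difference in attrition rates. The quantity that matters is, for each arm, the rate multiplied by the gap between how dropouts actually fared and what the model predicts for them. With equal rates, or more loss in HEP-NF, the trigger stays off. The estimate can still favour 3RP-NF in two ways: 3RP-NF dropouts may have lost their gains, or HEP-NF dropouts may have left because they felt well.

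The protocol's argument that control-heavy dropout is conservative carries its own condition, namely that such dropout reflects lack of efficacy. No planned analysis can establish this. Comparing completers with dropouts uses observed data only, and so cannot show how people fared after they left. If the pilot pattern recurred, the durability conclusions would rest on missing-at-random alone with up to 20% of outcomes missing.

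**Working it through.** **Inputs from the protocol.** 224 participants randomised 1:1, so 112 per arm (sections III and V); 5% loss by post-treatment and up to 20% by 12 months (VI.1), with 20% also used for 6 months (VI.3.1); margin 6.25 and one-sided 5% error (VI.3). Effective SDs from post-treatment to 6 months are 11.4 (Physical) and 10.0 (Psychological); from baseline to post-treatment they are 14.7 and 10.4 (VI.3.1). No 12-month SD is given, so I assume the 6-month values apply there too.

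**Reproducing the plan's figure.** Retained at follow-up: 224 × 0.80 = 179.2, against the stated 180, or 90 per arm. SE = SD × √(2/90) = 1.70 (SD 11.4) or 1.49 (SD 10.0). Power if the true difference is zero = Φ(6.25/SE − 1.645) = 97.9% or 99.5%, consistent with the stated 99%.

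**Bias.** Let p be an arm's dropout rate and δ its dropouts' true mean minus the missing-at-random prediction. The bias in the 3RP-NF minus HEP-NF difference is

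p(HEP) × δ(HEP) − p(3RP) × δ(3RP).

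The documents do not say how large δ is. I take 6.25 units, the protocol's estimated MCID, as an illustration.

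- 20% loss per arm, only 3RP-NF dropouts worse: 0.20 × 6.25 = 1.25 units. This is 1.25/1.70 = 0.74 SE to 1.25/1.49 = 0.84 SE.
- Post-treatment, 5% loss: 0.05 × 6.25 = 0.31 units. SE = 14.7 × √(2/106) = 2.02 (Physical) and 10.4 × √(2/106) = 1.43 (Psychological), so the bias is 0.15 to 0.22 SE.

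**False non-inferiority when the truth sits at the margin.** The rate is Φ(bias/SE − 1.645), with SE = SD × √(1/n(3RP) + 1/n(HEP)) and n = 112 × (1 − p). In each range the first figure is for SD 11.4 and the second for SD 10.0.

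| Dropout, 3RP-NF / HEP-NF | Assumed departure of 6.25 units | Trigger | Bias | False non-inferiority |
|---|---|---|---|---|
| 20% / 20% | 3RP-NF dropouts worse | off | +1.25 | 18-21% |
| 20% / 20% | dropouts in both arms worse | off | 0 | 5% |
| 15% / 25% | 3RP-NF dropouts worse | off | +0.94 | 14-15% |
| 15% / 25% | HEP-NF dropouts better | off | +1.56 | 23-27% |
| 15% / 25% | HEP-NF dropouts worse | off | −1.56 | 0.5-0.4% |
| 25% / 15% | 3RP-NF dropouts worse | on | +1.56 | 23-27% |

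**Tipping point.** With an observed difference of zero and only 3RP-NF dropouts worse, non-inferiority is lost when δ exceeds (6.25 − 1.645 × SE)/p(3RP) in size. At 20% / 20% (SE 1.703 and 1.494 with 89.6 per arm) this is 3.45/0.20 = 17 units to 3.79/0.20 = 19 units.

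**The case against.** A reader might infer that the rule leaves the most dangerous dropout pattern unexamined. The documents do not support that. Excess loss of poorly faring 3RP-NF participants is the obvious threat to a 3RP-NF durability claim, and it is what switches the analyses on. In the table, the covered case (23-27%) is at least as serious as any uncovered case with a departure in one arm. Nor is dropout wholly unexamined: patterns of missing data and completer/dropout differences are assessed in every case. Because post-test retention was 100% in the pilot, most later dropouts should have an observed post-test score. That helps describe them, although it cannot detect loss that is missing not at random.

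Two other stronger readings also fail. The 6- and 12-month results are not the trial's primary result, since section II makes post-intervention the primary time point. And the trigger is data-dependent but looks at attrition, not at quality-of-life scores.

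The protocol's rationale has substance. If HEP-NF dropouts do fare worse, the bias works against 3RP-NF and false non-inferiority falls to about 0.5%. The illustration is also severe: every 3RP-NF dropout falls a full 6.25 units below a prediction already conditioned on observed scores, while HEP-NF dropouts follow theirs exactly. The pilot is thin evidence on direction, with about ten people lost among 63 and no counts by arm.

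The ranges and grids of such analyses can properly be left to a statistical analysis plan. What stands is that the protocol itself states a restricting condition, and that the condition does not track the bias it is meant to guard against.

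**Conclusion.** The concern holds as a modest point about the secondary time points. Informative-dropout analyses are tied to one direction of attrition, while equal or control-heavy loss can also favour 3RP-NF. Under the stated assumptions (a 6.25-unit departure in 3RP-NF dropouts only, 20% loss per arm, truth at the margin), the error rate is about 18-21% instead of 5%, with nothing triggered. At post-treatment the effect is slight.

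The durability conclusion may well prove robust, since at 20% loss per arm and an observed difference of zero it takes a departure of nearly three margins or more (17/6.25 = 2.7; 19/6.25 = 3.0) to overturn it. Under the present rule, however, that robustness would be shown only if attrition happened to run one way.

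**What to change.** In section VI.1, delete the condition on higher 3RP-NF attrition. State that delta-adjusted (tipping-point) multiple imputation will be run whatever the attrition pattern, for both co-primary outcomes at 6 and 12 months and also at post-treatment, with deltas varied separately by arm. Deltas could start at 0 to −6.25 in 3RP-NF and 0 to +6.25 in HEP-NF, and be extended until the conclusion changes. Present control-heavy dropout as conservative only under the lack-of-efficacy assumption.

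Reference-based imputation is not needed. If it is added, specify it as jump-to-reference on outcome levels. Copying HEP-NF increments after post-test would pull the maintenance difference towards zero and so favour non-inferiority.

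The cost is one reworded sentence and a little more analysis work, with no new data and no added burden on participants.

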## V. STUDY PROCEDURES

Participants will be randomized 1:1 to 3RP-NF or HLI using a permuted-block randomization, stratified by diagnosis. Stratification ensures that an equal number of participants with NF1, NF2 and schwannomatosis are allocated to both treatments. Randomization will be generated by a computer.

We will use the same clinician/study therapist across the study conditions. Consideration was given to using different therapists for each arm to minimize potential contamination. However, observed study effects might be then attributable to clinician/therapist factors, and the study manuals are distinct. To deal with potential contamination, we will employ the audio-recording supervision and review as detailed below, including the use of checklists to document therapist fidelity to the intervention and also to prevent drift.

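### Section VI.2 lists homework completion, which is recorded after randomisation, among the baseline characteristics for the confounder check

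*Protocol*

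**What the plan says.** Section VI.2 of the protocol (Evaluating possible confounders) opens with a check of randomisation: "we will examine the equivalence of the random assignment of groups with regard to key baseline characteristics". The next sentence names what is compared: "This will involve assessment of the treatment groups on sociodemographic characteristics, psychosocial variables and homework completion". If differences of importance have arisen by chance, the protocol says "we will run analyses both with and without these variables as covariates to determine whether baseline differences may account for differences in outcomes".

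The list of measures in Section V gives homework a different place. Its entry reads "Patient Homework –weekly during intervention", and the progress note beneath it is labelled "adherence to treatment/skill consolidations/moderator". Only demographics are listed as collected before the intervention alone. The description of 3RP-NF in Section V (1.1) makes home practice part of the treatment: forms are handed in at each session, and obstacles to practice are discussed there.

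On the design, Section V randomises 1:1 "using a permuted-block randomization, stratified by diagnosis". The primary model in Section VI.3 is a shared-baseline linear mixed model with unstructured covariance, analysed by intention to treat. It names no homework term and no diagnosis term. Diagnosis enters a model in Section VI.4.2, where it is added to test moderation.

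**The concern.** A confounder check in a randomised trial asks whether a chance difference that existed before treatment could explain the result. Homework completion cannot answer that question, because it comes after assignment and may be affected by it. If the arms differ on it, the difference may itself be an effect of treatment. Adjusting for it then removes whatever part of the effect works through practice. It can also bring in bias from causes shared by homework and outcome, such as motivation.

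What is at stake is the reading of the comparison with and without covariates. A shift in the estimate after adjusting for homework would be reported as baseline differences accounting for the result, which would be a wrong inference.

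A smaller matter is that the trial stratifies by diagnosis, but the primary model as written does not use the stratum.

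**Working it through.** **1. The passages side by side**

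| Feature | Section VI.2 | Section V |
|---|---|---|
| Timing of homework | treated as a baseline characteristic | recorded weekly during the intervention |
| Role | possible confounder and covariate | adherence, part of the 3RP-NF sessions |

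The two cannot both hold. The timing in Section V is unambiguous, so the error lies in VI.2.

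**2. What adjusting for homework could do**

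The one input from the protocol is the effect of 6.25 units (the MCID, Section VI.3.1). All other inputs are assumed, because the protocol gives no homework data:
- d: difference in homework, 3RP-NF minus HEP-NF, from -0.5 to +0.5 SD.
- b: effect of 1 SD of homework on QoL change, 2 or 4 units.
- u: correlation of homework with an unmeasured common cause U, 0 or 0.4, where U adds 3 units per SD to the outcome.

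Model, with T = 1 for 3RP-NF and homework H of unit SD within arm:
- H = d·T + u·U + residual
- change = (6.25 - b·d)·T + b·H + 3·U + noise

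The total effect is (6.25 - b·d) + b·d = 6.25 by construction. Within arm, U has slope u on H, so the fitted homework coefficient is b + 3u and

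adjusted effect = 6.25 - d·(b + 3u).

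| d | b | u | Adjusted effect |
|---|---|---|---|
| +0.5 | 2 | 0 | 6.25 - 0.5 × 2 = 5.25 |
| +0.5 | 4 | 0 | 6.25 - 0.5 × 4 = 4.25 |
| +0.5 | 4 | 0.4 | 6.25 - 0.5 × 5.2 = 3.65 |
| -0.5 | 2 | 0 | 6.25 + 0.5 × 2 = 7.25 |
| -0.5 | 4 | 0 | 6.25 + 0.5 × 4 = 8.25 |
| -0.5 | 4 | 0.4 | 6.25 + 0.5 × 5.2 = 8.85 |

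Simulation with 400,000 participants per setting gave 3.64 and 8.85 for the two extreme rows. A true 6.25 can therefore appear as about 3.6 to 8.9. With d = 0 there is no shift.

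**3. The stratum**

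The plan's own figure comes first. Inputs are 6.25 units, SD 14.7, two-sided 0.025 (all Section VI.3.1), and 212 participants at post-treatment (Section VI.1), so 106 per arm.
- SE = 14.7 × √(2/106) = 2.019
- 6.25/2.019 = 3.095, and 3.095 - 2.241 = 0.854
- power = Φ(0.854) = 80.3%, so the stated 80% reproduces.

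If diagnosis explains a share R² of the variance of change (assumed), the SD becomes 14.7 × √(1 - R²):

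| R² | SD | Power |
|---|---|---|
| 0 | 14.70 | 80.3% |
| 2% | 14.55 | 81.2% |
| 5% | 14.33 | 82.5% |

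A simulation of post-treatment change used N = 212, the pilot mix of 71/19/10% and an assumed block size of 4. With 10,000 null runs per setting, the Monte Carlo SE is √(0.025 × 0.975/10,000) = 0.0016. Without the stratum term, type I error at nominal 0.025 was 0.022 at R² of 2% and 0.021 at 5%. With the term it was 0.023 and 0.025. Simulated power, from 5,000 runs, rose from 80.3% to 81.1% at R² of 2% and from 81.4% to 82.8% at 5%. Leaving the term out is conservative and costs little.

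**The case against.** The strongest reply is that the covariate rule is worded for chance differences present at baseline. Homework has no baseline value, so on a literal reading it never meets the trigger. That stands in part, since the text does not plainly commit the trial to adjusting for homework. But the covariates are called "these variables" by reference to a list that contains homework, so the section contradicts itself and needs correcting either way.

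A reader might infer four stronger things, none of which the documents support.
- **That the primary result would be adjusted for homework.** It would not. Superiority rests on the intention-to-treat mixed model, which names no such term, and the adjusted run is a check reported beside the unadjusted one.
- **That the arms are bound to differ, so that a real effect would look explained away.** HEP-NF leaves out the 3RP-NF skills, but that concerns the content of homework, not its completion. Section I (Study 5) reports that both pilot arms completed homework, with no rates by arm. A difference is possible, but its direction is unknown, and the bias can inflate as well as shrink the effect.
- **That a homework moderator analysis is planned.** The word appears once, in the measures list. Neither Aim 2 nor Section VI.4.2 includes homework among its moderators.
- **That omitting diagnosis endangers the type I error.** The omission is conservative. An analysis plan that is not shown could add the term, and the protocol gives no evidence that diagnosis predicts change, so the gain may be nil.

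**Conclusion.** "This will involve assessment of the treatment groups on sociodemographic characteristics, psychosocial variables and homework completion" is wrong as written for its last item. Homework completion follows randomisation and is part of the treatment, so it can be neither a baseline characteristic nor a confounder of the randomised comparison. The damage is confined to the check with and without covariates. No stated sample size, alpha, power or success rule changes.

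The size of the bias is unknown. The range of about 3.6 to 8.9 around a true 6.25 rests wholly on the assumed arm differences, homework effects and common cause set out above. It shows that the bias could matter and could go either way; it is not a forecast.

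The stratum is a minor improvement and not an error: 0 to about 2 power points for QoL Physical, on an assumed R² of 0 to 5%.

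**What to change.** - In Section VI.2, delete homework completion from the list of characteristics compared.
- Report homework completion by arm as adherence, in line with Section V.
- State that the check with and without covariates is limited to variables measured before randomisation.
- As an optional gain, add diagnosis (NF1, NF2, schwannomatosis) and diagnosis-by-visit to the primary model in Section VI.3 as fixed effects. The interaction is needed because a diagnosis main effect alone shifts all visits equally and explains none of the variation in change.

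The cost is protocol wording and one three-level factor with its visit interaction. All the data are already collected, and neither sample size nor alpha changes.
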